#### **10.1.3. Adverse Device Effect**

An Adverse Device Effect (ADE) is an adverse event related to the use of an investigational medical device (ISO 14155: 3.1). This includes adverse events resulting from insufficient or inadequate instructions for use, deployment, implantation, installation, or operation, or any malfunction of the investigational medical device. This definition also includes any event resulting from use error or from intentional misuse of the device under investigation.

#### **10.1.4. Serious Adverse Event**

A serious adverse event (SAE, ISO 14155, 3.45) is an adverse event that:

- led to a death
- led to a serious deterioration in the health of the participant, users, or other persons that either resulted in:
  - a life threatening illness or injury
  - a permanent impairment of a body structure or function including chronic diseases
  - in-patient hospitalisation or prolonged hospitalisation
  - medical or surgical intervention to prevent life-threatening illness or injury or permanent impairment to a body structure or a body function
- led to foetal distress, foetal death or a congenital abnormality or birth defect including physical or mental impairment

A planned hospitalisation for pre-existing condition, or a procedure required by the study protocol, without a serious deterioration in health, is not considered to be a serious adverse event.

More than one of the above criteria can be applicable to one event. Life-threatening in the definition of a serious adverse event or serious adverse reaction refers to an event in which the participant was at risk of death at the time of the event; it does not refer to an event which hypothetically might have caused death if it were more severe. Medical judgement should be exercised in deciding whether an adverse event or reaction is serious in other situations.

Important adverse events or reactions that are not immediately life-threatening or do not result in death or hospitalisation but may jeopardise the participant or may require intervention to prevent one of the other outcomes listed in the definition above, should also be considered serious.

#### **10.1.5. Serious Adverse Device Effect**

A Serious Adverse Device Effect (SADE; ISO 14155, 3.44) is an adverse device effect that has resulted in any of the consequences characteristic of a serious adverse event.

- An Unanticipated Serious Adverse Device Effect (USADE) is a serious adverse device effect which by its nature, incidence, severity or outcome has not been identified in the current version of the protocol or the risk analysis report (ISO 14155: 3.51).
- An Anticipated Serious Adverse Device Effect (ASADE) is a serious adverse device effect which by its nature, incidence, severity or outcome has been identified in the protocol or the risk analysis report.

#### 10.1.6. Device Deficiencies

A device deficiency is an inadequacy of a medical device with respect to its identity, quality, durability, reliability, usability, safety or performance, of an investigational device, including malfunction, user errors and inadequate information supplied by the manufacturer (Art. 2 Abs 59 MDR, ISO 14155: 3.19). Malfunction is the failure of an investigational device to perform in accordance with its intended purpose when used in accordance with the instructions for use (ISO14155: 3.33). The definition includes deficiencies related to the investigational medical device or the comparator medical device.

A device deficiency may lead to an Adverse Device Effect or Serious Adverse Device Effect (Art. 80 Abs 1 letter c MDR; ISO 14155). This includes any device deficiency that might have led to a serious adverse event if appropriate action had not been taken, intervention had not occurred, or circumstances had been less fortunate.

The following anticipated device deficiencies and device-related issues will not be recorded:

- Infusion set occlusion/leakage not leading to ketonaemia (<3mmol/L)
- Sensor failure due to significant over/under-reading (difference>3mmol/L) or detachment
- Premature interruption of sensor-life
- Battery lifespan deficiency due to inadequate charging or extensive wireless communication
- Closed-loop system error messages not needing system replacement
- Intermittent device communication failure not leading to system replacement

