### **3.3. Closed-loop insulin delivery**

The emergence of new technologies including continuous glucose monitors (CGM) (13), insulin pumps and sensor augmented pump therapy (SAP) (14-16) provides new opportunities to improve outcomes for people with diabetes. The most promising approach is closed-loop insulin therapy (17) which combines real-time CGM with insulin pump therapy to achieve glucose-responsive subcutaneous insulin delivery. The vital component of such a system, also known as an artificial pancreas (AP), is a control algorithm. The role of the control algorithm is to compute the amount of insulin to be delivered by the pump using the real-time sensor glucose levels.

The closed-loop approach has been successfully evaluated in children and adults with type 1 diabetes in controlled laboratory studies (18-20) and in home settings (21-26). The results

demonstrated improved glucose control and reduced risk of hypoglycaemia events. Psychosocial assessments supported acceptability and positive impact of this approach and hybrid closed-loop systems are now transforming the management of type 1 diabetes. A fully closed-loop approach to the management of type 2 diabetes has been evaluated in the inpatient setting (27-29), and in the home setting (30, 31), with results suggesting that this technology is a tangible option to improve glucose control in this population.

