## **10. Assessment and Reporting of Adverse Events**

### **10.1. Definitions**

#### **10.1.1. Reportable Adverse Events**

A reportable Adverse Event is any untoward medical occurrence that meets criteria for a serious adverse event or any unanticipated medical occurrence in a study participant that is study or device-related. Device deficiencies that could have led to a serious adverse device effect will also be reported (ISO 14155: 8.2.5 and 9.8).

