### **10.2.2. Recording and reporting of adverse events**

Throughout the course of the study, all efforts will be made to remain alert to possible adverse events or untoward findings. The first concern will be the safety of the participant, and appropriate medical intervention will be taken. The investigator will elicit reports of adverse events from the participant at each visit and complete adverse event forms. All AEs, including those the participant reports spontaneously, those the investigators observe, and those the participant reports in response to questions will be recorded on paper or electronic AE forms at each site within seven days of discovering the event. Furthermore, device deficiencies (DD) will also be collected, fully investigated and documented in the source document and appropriate CRF during the entire investigation period, i.e. from patient's informed consent until the final study visit.

- Documentation of AEs (including SAEs) by the PI includes diagnosis or symptoms, start and stop dates of event, event treatment, event resolution, assessment of seriousness and causal relationship to medical device and/or investigation procedure (ISO14155).
- Documentation of DDs by the PI includes description of event, start date, investigational device information, action taken with regard to the investigational device, and whether the DD led to an AE. The Sponsor shall review all DDs and determine and document in writing whether they could have led to a SAE (DD with SADE potential) (ISO14155).

The study investigator will assess the relationship of any adverse event to be device-related or unrelated by determining if there is a reasonable possibility that the adverse event may have been caused by the study device or study procedures. The individual investigator at each site will be responsible for managing all adverse events according to local protocols, and decide if reporting is required.

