#### **10.2.5. Recording and reporting of device deficiencies**

All device deficiencies will be documented throughout the study. The investigator at each site will be responsible for managing all device deficiencies and determine and document in writing whether they could have led to a serious adverse device effect.

All device deficiencies that might have led to a serious adverse device effect(s) if: suitable action had not been taken; intervention had not been made, or if circumstances had been less fortunate, must be reported to the Sponsor as for SAEs/SADEs.

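### Section 10.1.6 leaves listed device deficiencies unrecorded, including any sensor error above 3 mmol/L, while 10.2.2 and 10.2.5 require all deficiencies to be documented and assessed, so near misses can be lost

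*Protocol*

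**What the plan says.** Section 10.1.6 first defines device deficiencies broadly. The definition takes in any that might have led to a serious adverse event had action not been taken or had luck been worse. The section then states: "The following anticipated device deficiencies and device-related issues will not be recorded". Six items follow, among them "Sensor failure due to significant over/under-reading (difference>3mmol/L) or detachment", infusion-set occlusion or leakage without ketonaemia, and "Closed-loop system error messages not needing system replacement".

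The recording sections set a general rule. Section 10.2.5 states: "All device deficiencies will be documented throughout the study". It adds a written judgement by the investigator on SADE potential, and it requires deficiencies with that potential to go to the sponsor by the route used for serious events. Section 10.2.2 has deficiencies collected, investigated and entered in source and CRF, and continues: "The Sponsor shall review all DDs and determine and document in writing whether they could have led to a SAE". Section 10.1.1 adds: "Device deficiencies that could have led to a serious adverse device effect will also be reported". Neither 10.2.2 nor 10.2.5 mentions the list in 10.1.6 or makes an exception for it.

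**The concern.** The same event falls under two opposite instructions: do not record it, and document it with a written assessment. The conflict matters most for the sensor item. Under section 3.3 the control algorithm's role is to "compute the amount of insulin to be delivered by the pump using the real-time sensor glucose levels", and section 3.4 describes delivery in type 2 diabetes as fully automated with no mealtime bolus. A sensor that reads wrongly but keeps transmitting is therefore feeding the dosing calculation.

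At stake is the record of near misses, meaning deficiencies that caused no recordable harm but could have. With 15 sites in seven countries, some may follow 10.1.6 and others 10.2.5. The deficiency data would then depend on which paragraph a site reads.

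**Working it through.** The protocol states no figure to reproduce and the point rests on no calculation. The check is a comparison of text.

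**1. What limits each item on the 10.1.6 list?**

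| Item not recorded | Limit stated |
|---|---|
| Infusion-set occlusion or leakage | Only if no ketonaemia (below 3 mmol/L) |
| Sensor over- or under-reading above 3 mmol/L, or detachment | None on consequence |
| Early end of sensor life | None on consequence |
| Short battery life | By cause only |
| Closed-loop error messages | Only if the system need not be replaced |
| Intermittent communication failure | Only if the system is not replaced |

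Three of the six carry a limit tied to outcome or replacement. The sensor-reading item does not.

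**2. Do those limits match the reporting duty?** No. They ask what did happen (ketonaemia, replacement). Sections 10.1.1 and 10.2.5 ask what could have happened. An occlusion without ketonaemia may be exactly the near miss that the duty is meant to catch. Whether it is one is decided by an assessment, and non-recording comes before any assessment.

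**3. Does another form pick the event up?** Not always. Sections 10.1.2 and 10.2.3 exclude non-severe hypoglycaemia from adverse event recording, and 10.1.2 also excludes hyperglycaemia without significant ketonaemia.

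- Sensor error followed by a non-severe low: no deficiency form, no adverse event form.
- Occlusion followed by hyperglycaemia without significant ketonaemia: likewise neither.

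Uploaded CGM and pump data (11.1.4, 11.1.5) would still exist, but in the first case the sensor trace is itself the faulty measurement.

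**4. What is still captured?** Severe hypoglycaemia gets an adverse event form (10.2.3). Severe hypoglycaemia, ketoacidosis, adverse events and serious adverse events are tabulated for all participants (13.3). SADEs are part of the safety evaluation (9.2). The DSMB is informed of all serious adverse events and of unanticipated adverse device effects (10.6, 19.1).

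**5. Do other sections assume a complete record?** Yes. The study contacts in 8.5 are meant to record device deficiencies. Sections 10.2.4.2 (Switzerland) and 10.2.4.4 (Germany) have deficiencies assessed for serious potential, and the Swiss annual safety report is to list all of them.

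**Illustration only, with assumed values.** A true glucose of 3.4 mmol/L over-read by 3.1 mmol/L displays as 3.4 + 3.1 = 6.5 mmol/L, inside the 3.9 to 10.0 mmol/L target range. This shows why an error above the 3 mmol/L threshold cannot be assumed trivial. It says nothing about how often such errors occur.

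**The case against.** The best defence is that 10.1.6 is a definitions section. It settles which deficiencies enter the process, and 10.2.2 and 10.2.5 govern those that do. The protocol treats adverse events the same way: 10.1.2 lists what is not recorded and 10.2.2 then speaks of all adverse events. The listed items are routine and anticipated, and the duty to report SADE potential remains in force.

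This is a fair account of what was probably intended, and it shows that the repair is small. It does not remove the conflict. Section 10.1.6 itself calls the items device deficiencies. For hypoglycaemia the exemption is repeated in the recording section (10.2.3), but for deficiencies it is not. The duty to report potential also cannot operate on events that nobody writes down.

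Three stronger readings may tempt a reader, and the documents support none of them.

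- *The main failure modes of the system escape the safety evaluation.* They do not. Resulting harm is captured as in step 4 above, and infusion-set failures with ketonaemia and errors needing system replacement fall outside the list. Device deficiencies are not a named safety outcome in 9.2 or 13.3, so none is removed.
- *Under-recording favours the device.* No planned analysis compares deficiency counts between arms, and pump and closed-loop items have no counterpart in the control arm.
- *Time below 3.9 mmol/L is biased.* Sensor error affects that endpoint whether or not a form is completed. Both arms have the same sensor provision (12.4), and the listed item covers under-reading as well as over-reading.

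**Conclusion.** The point holds as an inconsistency in safety recording. If 10.1.6 is followed as written, near misses on the list go unrecorded and unassessed, contrary to 10.1.1, 10.2.2 and 10.2.5. The sensor-reading item is the clearest case. The loss is confined to deficiencies without recordable harm and does not touch the efficacy analyses.

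The number of events cannot be estimated, because the protocol gives no rate for any listed item. The exposed group in the closed-loop arm is the planned 112 participants over 26 weeks. The conclusion assumes that at least some listed deficiencies could have SADE potential. The risk analysis cited in 10.3.9 is not shown and might narrow that set, but 10.1.6 does not refer to it as the basis for the exemption.

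**What to change.** Reconcile 10.1.6 with 10.1.1, 10.2.2 and 10.2.5. State in 10.1.6 that the list of unrecorded items applies only to deficiencies with no potential for a SADE, and say this specifically for sensor over- or under-reading while the sensor is driving closed-loop. Cross-reference the exemption in 10.2.2 and 10.2.5, so that the words about all deficiencies carry the same scope throughout.

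The cost is an amendment of a few sentences and some extra deficiency forms at sites. A tick-box CRF item (type of deficiency, SADE potential yes or no) would keep that burden small. Recording every sensor error, tabulating deficiencies per person-month or sending all of them to the DSMB would be optional additions that the inconsistency does not require.

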#### 10.1.7. Adverse event intensity

| Intensity | Definition                                                                      |
|-----------|---------------------------------------------------------------------------------|
| Mild      | Patient is aware of signs and symptoms but they are easily tolerated            |
| Moderate  | Signs / symptoms cause sufficient discomfort to interfere with usual activities |
| Severe    | Patient is incapable to work or perform usual activities                        |

NB. The term “severe” is often used to describe the intensity (severity) of a specific event. This is not the same as ‘serious’, which is based on patient/event outcome or action criteria (see definition 10.1.4). For example, itching for several days may be rated as severe, but may not be clinically serious.

#### **10.1.8. Adverse event causality (MDCG 2020-10/1)**

| Intensity    | Definition                                                                                                                             |
|---------------------|-----------------------------------------------------------------------------------------------------------------------------------------------|
| Not related         | The relationship to the device or procedures can be excluded.                                                                                 |
| Possible            | The relationship with the use of the investigational device is weak but cannot be ruled out completely. Alternative causes are also possible. |
| Probable            | The relationship with the use of the investigational device seems relevant and/or the event cannot reasonably be explained by another cause.  |
| Causal Relationship | The serious event is associated with the investigational device or with procedures beyond reasonable doubt.                                   |

### **10.2. Recording and reporting of adverse events, serious adverse events and device deficiencies**

#### **10.2.1. Monitoring period of adverse events**

The period during which adverse events will be reported is defined as the period from the beginning of the study (obtaining informed consent) until 2 weeks after the end of the study participation (completion of the final study visit). Adverse events that continue after the participant’s discontinuation or completion of the study will be followed until their medical outcome is determined or until no further change in the condition is expected. The follow up of AEs may therefore extend after the end of the clinical investigation; however no new AEs will be reported after the trial reporting period.

### **10.2.2. Recording and reporting of adverse events**

Throughout the course of the study, all efforts will be made to remain alert to possible adverse events or untoward findings. The first concern will be the safety of the participant, and appropriate medical intervention will be taken. The investigator will elicit reports of adverse events from the participant at each visit and complete adverse event forms. All AEs, including those the participant reports spontaneously, those the investigators observe, and those the participant reports in response to questions will be recorded on paper or electronic AE forms at each site within seven days of discovering the event. Furthermore, device deficiencies (DD) will also be collected, fully investigated and documented in the source document and appropriate CRF during the entire investigation period, i.e. from patient's informed consent until the final study visit.

- Documentation of AEs (including SAEs) by the PI includes diagnosis or symptoms, start and stop dates of event, event treatment, event resolution, assessment of seriousness and causal relationship to medical device and/or investigation procedure (ISO14155).
- Documentation of DDs by the PI includes description of event, start date, investigational device information, action taken with regard to the investigational device, and whether the DD led to an AE. The Sponsor shall review all DDs and determine and document in writing whether they could have led to a SAE (DD with SADE potential) (ISO14155).

The study investigator will assess the relationship of any adverse event to be device-related or unrelated by determining if there is a reasonable possibility that the adverse event may have been caused by the study device or study procedures. The individual investigator at each site will be responsible for managing all adverse events according to local protocols, and decide if reporting is required.

### **10.2.3. Severe hypoglycaemia**

Severe hypoglycaemia will be defined as an event requiring assistance of another person due to altered consciousness to actively administer carbohydrate, glucagon, or other resuscitative actions. This means that the participant is impaired cognitively to the point that he/she is unable to treat him or herself, is unable to verbalize his or her needs, is incoherent, disoriented, and/or combative, or experiences seizure or coma. If plasma glucose measurements are not available during such an event, neurological recovery attributable to the restoration of plasma glucose to normal is considered sufficient evidence that the event was induced by a low plasma glucose concentration.

Severe hypoglycaemia will be regarded as a foreseeable adverse event and an adverse event form will be completed. Severe hypoglycaemia is not necessarily a serious adverse event and hence may

not require immediate reporting to the Sponsor. Non-severe hypoglycaemia will not be reported or considered an adverse event.

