#### **10.1.2. Adverse Events**

An adverse event (AE) is any untoward medical occurrence, unintended disease or injury, or untoward clinical signs (including abnormal laboratory findings) in a participant, users or other persons, who has received an investigational device, whether or not related to the investigational medical device (ISO 14155: 3.2). This definition includes events related to the device under investigation or the comparator or to the study procedures. The following anticipated adverse events will not be recorded:

- Non clinically significant skin reactions as judged by investigator
- Pre-existing medical conditions
- New illnesses or conditions not requiring concomitant medication or medical intervention/procedures
- Non severe hypoglycaemia
- Hyperglycaemia without significant ketonaemia (<3mmol/L)

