### **13.3. Safety Evaluation**

Safety data including severe hypoglycaemia events will be tabulated for all participants, including drop-outs and withdrawals, irrespective of whether CGM data are available and irrespective of whether closed-loop was operational. All adverse events will be listed for the entire study duration.

For each of the following safety outcomes, mean  $\pm$  SD or summary statistics appropriate to the distribution will be tabulated by treatment group:

- Number of severe hypoglycaemia events
- Number of participants with any severe hypoglycaemia event
- Number of diabetic ketoacidosis events
- Number of participants with any diabetic ketoacidosis event
- Number of adverse events per participant
- Number of serious adverse events per participant

For severe hypoglycaemia (if enough events), the event rates will be compared using a repeated measures regression model.

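### The rule against recording non-severe hypoglycaemia has no exception for serious episodes and conflicts with the protocol's own SAE reporting rules

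*Protocol*

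**What the plan says.** Section 10.2.3 sets the boundary of severity: "Severe hypoglycaemia will be defined as an event requiring assistance of another person due to altered consciousness". The text that follows explains this as cognitive impairment that prevents self-treatment. Hospital admission plays no part in the definition. The section then says that "Severe hypoglycaemia is not necessarily a serious adverse event", and closes with the rule at issue: "Non-severe hypoglycaemia will not be reported or considered an adverse event".

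Section 10.1.2 gives a list of anticipated adverse events that are not to be recorded. One item is "Non severe hypoglycaemia", with no qualification.

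Section 10.1.1 includes among reportable events "any untoward medical occurrence that meets criteria for a serious adverse event". Section 10.1.4 defines an SAE as an adverse event with certain outcomes. One of these, under the heading of a serious deterioration in health, is "in-patient hospitalisation or prolonged hospitalisation".

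Section 13.3 tabulates by treatment group, among other items, "Number of serious adverse events per participant". Section 9.2 includes SAEs and SADEs in the safety evaluation. Sections 10.6 and 19.1 have the data safety monitoring board informed of all SAEs.

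**The concern.** Hypoglycaemia is central to the safety objective of this trial, which tests an automated insulin-dosing device. The protocol decides whether a hypoglycaemic episode enters adverse event recording by a severity label based on consciousness, and does not ask whether the episode was serious. Elsewhere it makes seriousness, judged by outcome, the ground for reporting.

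The two rules collide for an episode without altered consciousness that nevertheless leads to serious deterioration with admission. One set of sections tells the site not to record it, and another tells the site to report it. The number of SAEs per participant is compared between arms, and SAE status drives notification of the sponsor and the monitoring board. Both would then depend on which sentence a site happens to follow. The trial has 15 sites in seven countries, and section 10.2.2 leaves the individual investigator to decide whether reporting is required, so uniform practice should not be assumed.

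**Working it through.** No arithmetic applies. The check traces one hypothetical episode through the definitions: hypoglycaemia without altered consciousness, leading to serious deterioration and in-patient admission.

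**Reading A, starting from 10.2.3**

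1. The episode does not meet the definition of severe hypoglycaemia, because consciousness is not altered.
2. By the closing sentence of 10.2.3 it is not an adverse event and is not reported. Section 10.1.2 adds that it is not recorded.
3. Under 10.1.4 an SAE is a kind of adverse event, so it is not an SAE.
4. Under 10.1.3 an adverse device effect is an adverse event related to the device, and under 10.1.5 a SADE is an adverse device effect with serious consequences. It is therefore neither of these.
5. Result: no entry in the SAE tabulation of 13.3 or the SADE data of 9.2, and no SAE notice to the monitoring board.

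**Reading B, starting from 10.1.1**

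1. The episode is an untoward medical occurrence.
2. It meets the hospitalisation criterion of 10.1.4, given the serious deterioration assumed.
3. By 10.1.1 it is reportable. In the UK, 10.2.4.1 sends every SAE to the sponsor, whether anticipated or not.
4. Result: it is counted and notified.

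**Is there a tie-break?** Neither 10.2.3 nor the list item in 10.1.2 says what happens if the episode is serious, and no section says which rule prevails.

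**Do 10.1.2 and 10.2.3 agree with each other?** They do not. Section 10.1.2 places non-severe hypoglycaemia among anticipated adverse events that go unrecorded, so there it is an adverse event. Section 10.2.3 says that it is not one.

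**Is it a deliberate choice?** The neighbouring text suggests a drafting gap. Three of the other four items in the 10.1.2 list are limited by clinical consequence: skin reactions that are not clinically significant, new illnesses needing no medication or intervention, and hyperglycaemia without significant ketonaemia. The hypoglycaemia item is limited only by the severity label. Section 10.2.3 itself keeps severity and seriousness apart, but in one direction only: a severe event need not be serious. It does not address a serious event that is not severe.

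**The case against.** The strongest reply is that the protocol, read as a whole, already captures such an episode. Section 10.1.1 starts from an occurrence and does not require a recorded adverse event; section 10.1.2 treats the episode as an adverse event; and section 10.1.4 adds that events which may jeopardise the participant should be considered serious. This stands as far as it goes. A reader might infer from 10.2.3 that a non-severe episode is shut out of SAE status altogether, and the documents do not support that, because these other sections point the opposite way. What remains is a contradiction that the protocol does not resolve.

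Secondly, admission alone does not make an SAE. In 10.1.4 hospitalisation sits under serious deterioration in health, and the section calls for medical judgement. That is correct, and the point is limited to episodes where that judgement is positive.

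Thirdly, a reader might see a conflict with 10.1.7, which separates severe from serious and describes the latter as one "which is based on patient/event outcome or action criteria". That section grades the intensity of adverse events by interference with usual activities, whereas severe hypoglycaemia is a separately defined clinical event. The point does not rest on it.

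Fourthly, other routes could pick up the episode. Over-delivery of insulin through malfunction or user error is a device deficiency under 10.1.6, and 10.2.5 requires deficiencies that might have led to a SADE to be reported to the sponsor. CGM time below range is analysed in both arms. These routes help but are not reliable substitutes. Section 10.1.6 excludes some causes from recording, including sensor misreading by more than 3 mmol/L, and CGM metrics show low glucose but not the admission.

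**Conclusion.** The point holds as an unresolved contradiction. Sections 10.2.3 and 10.1.2 exclude non-severe hypoglycaemia from reporting and recording without an exception for serious episodes, while 10.1.1 and 10.1.4 would make a serious one reportable. A site that follows 10.2.3 as written would omit an event that a site following 10.1.1 would report.

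The affected group is probably small: it needs serious deterioration with admission but without altered consciousness requiring another person's help. Admissions with such impairment count as severe and get an adverse event form. A reader might be tempted to scale up the rate in section 3.2 of 23 mild to moderate episodes per insulin-treated patient per year. The documents do not support an estimate on that basis. They give no admission rate, and the 3.2 figure counts episodes needing no third-party help, which is not the same class as non-severe in 10.2.3. The conclusion does not depend on the number. It assumes only that such an admission can occur and that sites apply the text as written.

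**What to change.** Reconcile the passages with the same exception in two places. In 10.2.3, replace the closing rule with: *Non-severe hypoglycaemia is not recorded as an adverse event unless it meets a criterion in 10.1.4, in which case it is recorded and reported as an SAE (and as a SADE if device-related).* Attach the same exception to the hypoglycaemia item in the 10.1.2 list. This also removes the disagreement between the two sections over whether a serious episode is an adverse event.

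The change concerns recording and reporting only. It leaves routine non-severe episodes unrecorded and does not touch treatment. It costs one clause in each of two sections, a line of CRF guidance for sites, and a few additional SAE forms.
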